### 5.3 LIFESTYLE CONSIDERATIONS

Not applicable.

### 5.4 SCREEN FAILURES

Screen failures are defined as participants who consent to participate in the clinical trial but are not subsequently randomly assigned to the study intervention or entered in the study. A minimal set of screen failure information is required to ensure transparent reporting of screen failure participants, to meet the Consolidated Standards of Reporting Trials (CONSORT) publishing requirements and to

respond to queries from regulatory authorities. Minimal information includes demography, screen failure details, eligibility criteria, and any serious adverse event (SAE).

## 5.5 STRATEGIES FOR RECRUITMENT AND RETENTION

### ***Recruitment Plan***

Participants will be recruited from patients who present to the emergency or urgent care department with a distal radius fracture. A hand surgery consult will be requested. If the consulting physician or PA determines that surgical fixation will be necessary, the patient will be placed in a splint and an appointment will be scheduled at the next hand surgery clinic per institutional standard practice. When the patient is seen in the hand surgery clinic, either the hand surgeon or PA will confirm the patient's eligibility for surgery and the study and will explain the study using the provided script (MOOP Section G4). If the patient is interested in participating, a Research Coordinator will meet with the patient, explain the study further, if necessary, and obtain informed consent

### **Recruitment Goals: Randomized Patients**

Year 1 (01/01/12-12/31/12): 14 patients

Year 2 (01/01/13-12/31/13): 14 patients (28 patients total)

Year 3 (01/01/14-06/30/14): 8 patients (36 patients total)

An addition 12 observational patients should also be recruited at a pace of 3 randomized patients to every 1 observational patient

### ***Screening***

Because emergency department flow and hand clinic scheduling vary from site to site, each site will be responsible for developing a unique system to screen and recruit eligible patients. Research personnel can expedite the recruitment process by pre-screening patients' emergency department records for mentions of prior DRFs to the same wrist, neurologic disorders affecting hand, wrist or arm sensation or movement, dementia, Alzheimer's Disease or other serious psychiatric disorders or current substance abuse. Previous medical records may be used as well. When the patient presents to clinic research personnel will assess the remaining eligibility criteria. Outcomes of eligibility screening will be recorded via the online Inclusion/Exclusion Criteria form (MOOP Section Q2).

### ***Inclusion/Exclusion Criteria Form***

For every patient who meets the initial inclusion criteria (a patient over the age of 60 years with a closed, unilateral distal radius fracture) an Inclusion/Exclusion Criteria form will be completed (MOOP Section Q2). Research staff will enter: the date the patient was screened, age, gender, race/ethnicity, eligibility status (eligible/ineligible) and participation status (eligible and enrolled / eligible and refused to provide consent). Research Coordinators should provide a brief description of the reason the patient is ineligible or why the patient refused to provide consent (if known). It should also be noted if the patient solicited advice from the surgeon as to the best treatment method, as this may be the reason for refusal to provide consent. Inclusion/Exclusion Criteria forms should be entered into REDCap on at least a bimonthly basis.

## 6 STUDY INTERVENTION

### 6.1 STUDY INTERVENTION(S) ADMINISTRATION

#### 6.1.1 STUDY INTERVENTION DESCRIPTION

- Open reduction and internal fixation with a volar locking plating system
- Closed reduction and external fixation with a bridging fixator with or without the use of supplementary k-wire fixation
- Closed reduction and percutaneous pinning with k-wires
- Closed reduction and casting or splinting

Details of the study interventions are provided in the MOOP Section K

#### 6.1.2 DOSING AND ADMINISTRATION

Not applicable.

### 6.2 PREPARATION/HANDLING/STORAGE/ACCOUNTABILITY

#### 6.2.1 ACQUISITION AND ACCOUNTABILITY

Surgeons will use the brand and type of plates and fixators of their choice provided by their institution. Brand and type information should be recorded on the Surgery Data Form (MOOP Section Q2).

#### 6.2.2 FORMULATION, APPEARANCE, PACKAGING, AND LABELING

Not applicable.

#### 6.2.3 PRODUCT STORAGE AND STABILITY

Not applicable.

#### 6.2.4 PREPARATION

Not applicable.

### 6.3 MEASURES TO MINIMIZE BIAS: RANDOMIZATION AND BLINDING

#### **Randomization Plan**

Randomization will be stratified by site.

#### **Process Responsibilities**

The Coordinating Center, in conjunction with Michigan Institute for Clinical and Health Research (MICHHR), is responsible for maintaining the randomization website and ensuring its accuracy. The Clinical Sites are responsible for retrieving randomization assignments from the website. This includes assuring that the correct information is entered and properly recording and relaying the randomization assignment and reporting any problems experienced with the site to the Coordinating Center.

It is important to note that once a patient has been randomized they should be followed until they have completed the 24-month follow-up visit or they withdraw their consent. This applies to all patients including those that have a different procedure than the one to which they were randomized.

#### ***Procedure for Randomizing a Participant***

Randomization should only be performed once all eligibility criteria have been assessed (Section 5) and the Inclusion/Exclusion form and the Mini Mental Status Exam (MOOP Section Q2) have been completed. Patients must provide informed consent form prior to randomization as well. The participant should be randomized to receive one of the three fixation techniques as soon as possible so that he/she may schedule surgery, receive pre-operative instructions and have any questions answered.

A Research Coordinator at each Clinical Site will login to the Treatment Assignment Tool – University of Michigan (TATUM) website (<https://michrapps.med.umich.edu/tatum/>) with their UM uniusername/username and Level 1 password (or UM Friend Account email and Level 1 password). Please enter the participant's StudyID and click "Retrieve Treatment" and "Okay" to confirm that you wish to randomize a participant. A screen will appear with the participants StudyID, Randomized ID and the Treatment Group. (See MOOP Appendix 5 for TATUM User Guide) Please record this information for entry in REDCap in the Study Arm form. An automatically generated email will be sent to the Coordinating Center and to the Clinical Site. Once the randomization assignment has been retrieved, the researcher will notify the surgery scheduler and record this information in the participant's study file.

The surgery scheduler should make every attempt to schedule the procedure without the surgeon knowing the exact procedure to be performed. Methods for doing this will vary from site to site; at the University of Michigan this will be achieved by scheduling the procedure as a "WRIST distal radius fixation." Surgical staff will prepare materials for each of the three procedures. No more than 24 hours before the procedure the surgeon should be informed of which procedure the patient was randomized to. This should be done using 2 methods, in case one method fails. These methods may include presenting an envelope to the surgeon, email, text message, or contacting the surgery scheduler to reveal the procedure in the schedule.

#### **6.4 STUDY INTERVENTION COMPLIANCE**

The PI is responsible for informing the participant of the procedure to which he/she was randomized and should be available to answer any questions the participant may have.

Each participant should receive the procedure to which her/she was randomized. In the event that the participant does not receive the randomized procedure, for whatever reason, the Protocol Deviation Form (MOOP Section Q2) should be completed and the Coordinating Center should be notified within 48 hours.

As soon as possible following surgery, the PI should complete the Surgery Data Form (MOOP Section Q2). Data should be derived from OR or anesthesiology records for accuracy and SHOULD NOT be estimated.

## 6.5 CONCOMITANT THERAPY

Not applicable.

### 6.5.1 RESCUE MEDICINE

Not applicable.

## 7 STUDY INTERVENTION DISCONTINUATION AND PARTICIPANT DISCONTINUATION/WITHDRAWAL

### 7.1 DISCONTINUATION OF STUDY INTERVENTION

Participant cross-over, for any reason, should be reported to the Coordinating Center in the same manner. The Protocol Deviation log (MOOP Section Q2) should be completed and the Coordinating Center should be notified within 24 hours.

Cross-over does not mean discontinuation from the study, and remaining study assessment should be completed as indicated by the study protocol.

### 7.2 PARTICIPANT DISCONTINUATION/WITHDRAWAL FROM THE STUDY

Participants are free to withdraw from participation in the study at any time upon request.

An investigator may discontinue or withdraw a participant from the study for the following reasons:

- If any clinical adverse event (AE), laboratory abnormality, or other medical condition or situation occurs such that continued participation in the study would not be in the best interest of the participant
- New disease or condition or worsening of existing disease or condition that makes it impossible for the participants to complete follow-up assessments (e.g. participant enters hospice/comfort care)

The reason for participant discontinuation or withdrawal from the study should be communicated to the Coordinating Center as soon as possible.

### 7.3 LOST TO FOLLOW-UP

A participant will be considered lost to follow-up if he or she fails to return for 24-month follow-up and is unable to be contacted by the study site staff.

The following actions must be taken if a participant fails to return to the clinic for a required study visit:

- The site will attempt to contact the participant and reschedule the missed visit within the study window (Section 5.5) and counsel the participant on the importance of maintaining the assigned visit schedule and ascertain if the participant wishes to and/or should continue in the study.
- Before a participant is deemed lost to follow-up, the investigator or designee will make every effort to regain contact with the participant including phone, mail, email, or communication through EMR.
- If the participant is willing to continue participation, but will not agree to return to clinic study surveys can be completed by mail, email, or phone.
- Should the participant continue to be unreachable, he or she will be entered as terminated with a primary reason of lost to follow-up.

## 8 STUDY ASSESSMENTS AND PROCEDURES

### 8.1 EFFICACY ASSESSMENTS

#### 8.1.1 TIMELINE AND SCHEDULE OF VISITS

See section 1.3 Schedule of Activities

#### 8.1.2 SCREENING EVALUATION

##### Screening

For every patient who meets the initial inclusion criteria (a patient over the age of 60 years with a closed, unilateral distal radius fracture) an Inclusion/Exclusion Criteria form will be completed (MOOP Section Q2). Research staff will enter: the date the patient was screened, age, gender, race/ethnicity, eligibility status (eligible/ineligible) and participation status (eligible and enrolled / eligible and refused to provide consent). Research Coordinators should provide a brief description of the reason the patient is ineligible or why the patient refused to provide consent (if known). It should also be noted if the patient solicited advice from the surgeon as to the best treatment method, as this may be the reason for refusal to provide consent. Inclusion/Exclusion Criteria forms should be entered into REDCap on at least a bimonthly basis.

##### Screening Period

Radiographic inclusion criteria may be evaluated pre- or post-reduction. Patients who meet all inclusion/exclusion criteria, including radiographic criteria, pre-reduction may be eligible for the study in two manners. Patients whose post-reduction x-rays indicate unacceptable reduction are eligible immediately. Patients whose post-reduction x-rays indicate acceptable reduction are eligible if x-rays indicate an unacceptable reduction

During screening, patient's eligibility will be assessed based on the inclusion and exclusion criteria as described in Sections 5.1 and 5.2.

---

### 8.1.3 ENROLLMENT AND BASELINE ASSESSMENTS

#### Enrollment

Our enrollment date is when the screening criteria are met and informed consent is signed by the patient.

#### Consenting Procedure

This study has a single informed consent form that describes both the screening and study procedures.

The Research Coordinator at each site will explain the study, review study requirements and emphasize the voluntary nature of participation to potential participants in detail. Additionally, the patient will also be told, as stated in the informed consent document, that non-participation will not affect his/her medical care in any way. The Research Coordinator will briefly detail the casting and other three procedures, in plain language, and explain that the procedures may be equally affective at repairing his/her distal radius fracture and that there is no “best” treatment. The Research Coordinator will briefly explain the randomization process and follow-up measures. Finally, the Research Coordinator will tell the patient that he/she will be compensated \$20 per follow-up assessment he/she completes, for a total of \$140.

A written comprehensive informed consent document will be used. Each institution will use its own informed consent document and follow its own policies to obtain informed consent. Once the patient has fully read the informed consent document and all concerns have been addressed, the patient may sign the document. Each participant will also receive a copy of the informed consent document for his/her records.

The signed informed consent form should be kept by each Clinical Site in their locked participant study files for a period of at least three years or longer if required by the Clinical Site’s IRB. Copies should be transmitted to the Coordinating Center via email, fax or mail on at least a monthly basis.

#### Baseline Assessments

X-ray: An X-ray of the patient’s fractured arm will be done.

Mini Mental State Examination: For this exam the following supplies are needed: a blank sheet of paper, a note card with the words “Close your eyes” printed clearly and a pen. The participant should be seated and asked to perform the various tasks that comprise the MMSE. A score will be calculated immediately. Patients with a score of 24 or below are considered ineligible

Participant Demographics: Data collected will include date of birth, gender, hand dominance, income and occupation. Injury data will include date of injury, date of surgery, injured arm, AO classification of

761 fracture, mechanism of injury, associated injuries, and any pre-existing upper extremity trauma or  
762 impairment.

763 Comorbidity checklist: It is a self-administered comorbidity questionnaire that the patient answers and  
764 will include information on patient's medical conditions such as heart disease, diabetes, or other  
765 medical problems.

766 RAPA: Rapid Assessment of Physical activity is a questionnaire about the amount and intensity of  
767 physical activity patients usually do. The RAPA is a 9 question survey that has been validated for use in  
768 adults over 50 years of age and has shown better sensitivity and specificity than other frequently used  
769 assessments of physical activity.

770 SF-36: Short Form (36) is a survey of patients' health to assess their health status.

771 Pain Domain of MHQ: A questionnaire to assess the amount of pain the patients had in their hand or  
772 wrist during the past week.

773 Participant payment: upon completion of consenting and enrollment the study participant will be paid  
774 \$20.

775 Adverse event and protocol deviation information will be collected if necessary during the visit.

---

776 **8.1.4 FOLLOW-UP ASSESSMENTS**

777 Visit 3: Scheduled at 2 weeks after the surgery or closed reduction

- 778 ○ X-Ray
- 779 ○ SF-36
- 780 ○ General Health Questionnaire
- 781 ○ Fingertip to palmar Crease Distance Form
- 782 ○ Complication Checklist
- 783 ○ Hand Therapy Data form
- 784 ○ Pain Domain of MHQ
- 785 ○ Hand function Data Form
- 786 ○ Participant payment
- 787 ○ Adverse Event collection
- 788 ○ Protocol deviation collection

789

790 Visit 4: Scheduled at 6 weeks following surgery or closed reduction

- 791 ○ X-Ray
- 792 ○ SF-36
- 793 ○ General Health Questionnaire
- 794 ○ Fingertip to palmar Crease Distance Form
- 795 ○ Complication Checklist
- 796 ○ Hand Therapy Data form
- 797 ○ MHQ(all domains)
- 798 ○ Hand function Data Form
- 799 ○ Participant payment

- 800                   ○ Adverse Event collection
- 801                   ○ Protocol deviation collection
- 802
- 803
- 804   Visit 5: Scheduled at 3months following surgery or closed reduction
- 805   Visit 6: Scheduled at 6 months following surgery or closed reduction
- 806   Visit 7: Scheduled at 12 months following surgery or closed reduction
- 807   Visit 8: Scheduled at 24 months following surgery or closed reduction (additional assessment of RAPA
- 808   will be done at this visit)
- 809                   ○ X-Ray
- 810                   ○ SF-36
- 811                   ○ General Health Questionnaire
- 812                   ○ Complication Checklist
- 813                   ○ Hand Therapy Data form
- 814                   ○ MHQ(all domains)
- 815                   ○ Hand function Data Form
- 816                   ○ Participant payment
- 817                   ○ Adverse Event collection
- 818                   ○ Protocol deviation collection

---

#### 819   8.1.5   FINAL EVALUATION

820   The 8th visit scheduled at 24 weeks following surgery or closed reduction is the final evaluation visit.

821   If the participant is not able to be evaluated within the appropriate time period, the reason should be  
822   noted in the comments section of the participant appointment log and the participant is considered lost  
823   to follow-up for that visit. If possible, the MHQ, SF-36 and RAPA, along with a postage paid envelope,  
824   should be sent to the participant. Despite missing one follow-up visit, the participant is still considered  
825   to be actively enrolled in the study and should be followed up for future visits.

826   Each participant should be reminded at the end of every visit when he/she will need to be seen again  
827   (i.e. "We'll see you in 6 months.") and should schedule an appointment, if possible. If a participant has  
828   not made a clinic appointment within 2 weeks of his/her follow-up date, a member of the research team  
829   should contact the participant via phone to schedule an appointment. The participant should be  
830   reminded that he/she is a valuable member of the research team and that participation is very  
831   important. A participant is considered to be active and should be reminded to return for follow-up  
832   assessment unless he/she chooses to withdraw from the study.

833   In an effort to collected as much data as possible, participants who were enrolled in the study at the  
834   time of their 24-month assessment and who did not complete the assessment will be contacted at the  
835   end of the study (Early 2019). Traditional 24 month surveys (MHQ, SF-36, and RAPA) will be sent to  
836   participants via postal mail.

837

## 8.2 SAFETY AND OTHER ASSESSMENTS

Not applicable.

## 8.3 ADVERSE EVENTS AND SERIOUS ADVERSE EVENTS

### 8.3.1 DEFINITION OF ADVERSE EVENTS (AE)

The NIH defines an AE as any unfavorable and unintended diagnosis, symptom, sign (including an abnormal laboratory finding), syndrome, or disease, which may or may not be related to the intervention. AEs include any new events not present during the pre-intervention period or events that were present during the pre-intervention period which has increased in severity. Sites should also check their IRB's for site-specific definitions and further guidance.

### 8.3.2 DEFINITION OF SERIOUS ADVERSE EVENTS (SAE)

The NIH defines an SAE as any untoward medical occurrence that results in death, is life-threatening, requires or prolongs hospitalization, causes persistent or significant disability/incapacity, results in congenital anomalies/birth defects, or, in the opinion of the investigators, represents other significant hazards or potentially serious harm to research participants or others. Sites should also check their IRB's for site-specific definitions and further guidance.

### 8.3.3 CLASSIFICATION OF AN ADVERSE EVENT

#### 8.3.3.1 SEVERITY OF EVENT

For adverse events (AEs) the following guidelines will be used to describe severity.

- **Mild** – symptoms, no specific treatment
- **Moderate** – diagnostic procedure, specific diagnosis, and/or nonsurgical treatment
- **Severe** – surgical treatment required

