## 2.3 RISK/BENEFIT ASSESSMENT

### 2.3.1 KNOWN POTENTIAL RISKS

All randomized patients may encounter the risks of anesthesia, which are RARE. These include: damage to teeth, mouth, throat or vocal cords, nerve or eye damage, drug reaction, slowing or stopping of breathing, failure of the anesthetic or sedation analgesia, cardiac arrest, risks that cannot be predicted, permanent disability or even death.

All randomized patients may encounter the general risks of distal radius fracture repair surgery, which are INFREQUENT. These include infection, pain, bleeding, persistent scar, deformity, nerve injury, tendon injury, decreased range of motion, malunion or nonunion, future arthritis (if fracture involves joint) and the need for further surgery.

All randomized patients may encounter the risk that the technique that the subject is randomized to will not be the appropriate one for them and the results inferior to those chosen outside the research context. This risk is RARE. All three techniques are considered standard procedures in the treatment of DRFs. All the surgeons participating in the study are experts in the treatment of DRFs and are equally comfortable performing each technique.

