##### Internal Fixation

Wound infection requiring antibiotics: INFREQUENT

Painful hardware requiring removal: RARE

We will try to avoid all risks associated with surgery by employing best practices regarding pre-operative risk screening, infection control, and all other aspects of the surgical process.

All patients may encounter the risk of loss of privacy or confidentiality. This risk is RARE. All research personnel involved in any way with this project will have completed training in the protection of human research participants, per the guidelines issued by the U.S. Department of Health and Human Services, Office for Human Research Protection. Participants will be assigned a StudyID and only the site that enrolled each participant will have a key to match StudyID to participants name or other identifying information. Online data entry systems will be password protected and the Coordinating Center will issues password on an individual basis. Study data will

be stored on encrypted servers and accessed via password protected computers. Hard copies of study documents will be kept in locked cabinets in locked offices.

All patients may encounter the risk of inconvenience, which is RARE. We will try to avoid this by delivering surveys to patient to complete in the exam room prior to seeing the surgeon whenever possible. We will also perform functional testing in an efficient manner.

---

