### 9.4.2 ANALYSIS OF THE PRIMARY EFFICACY ENDPOINT(S)

**Aim 1:** *To compare 12-month post-surgical outcomes of elderly DRFs treated with VLPS with CRP and EFP.* Primary outcome will be the summary score of the MHQ. We will report means for each group and the mean difference between pairs of each group, along with their 95% confidence intervals. The primary outcome will be compared using a linear mixed-effects model to address the hierarchical nature of the data. The model will include surgeons nested within site and sites as random effects, fracture severity group indicator effect and two indicators for EFP and CRP groups. The surgical procedure indicators will each estimate the difference between EFP to VLPS and CRP to VLPS. We will also obtain covariate adjusted estimates of the between group differences; the covariates will be determined by the baseline analyses and will likely include age, baseline MHQ score, dominance of the injured hand and baseline RAPA score. Similar analyses will be done using other secondary outcome variables, including grip strength. We will also calculate MHQ score and grip strength as the difference (and %) of the uninjured hand scores. These measures may better reflect recovery because the uninjured hand can give a proxy measure of the patient-specific maximum achievable outcome. Analysis of complications will depend on how often they occur. For example, if the combined complications are rare, we will dichotomize them as present/absent and use a generalized linear mixed-effects model with logit link to compare the odds of complication between VLPS/EFP and between VLPS/CRP, while adjusting for within surgeon and site correlation. If the number of complications is substantial, we will use a count data model such as generalized linear model with log link to make the between-group comparison.

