### 10.1.6 DATA HANDLING AND RECORD KEEPING

#### 10.1.6.1 DATA COLLECTION AND MANAGEMENT RESPONSIBILITIES

#### 10.1.6.2 DATA COLLECTION FORMS

From each participant, data forms such as, Participant Demographic Questionnaire, RAPA, SF-36, MHQ, Hand Function Data form will be collected by the study coordinator at every visit. The surgeon will complete the Surgery Data form after surgery and complication checklist at every visit after surgery and these forms will also be collected by study coordinator.

The investigators will make every effort to preserve the study subjects' confidentiality. No one other than study personnel will have access to the study participants' records. Precautions will be taken to ensure that the records are in a locked cabinet. Records will not have the subjects' names listed on them, but instead an identification number will be assign to each subject, which only the investigators and study coordinators will be able to link to subject names. The subjects will also not be identified in any reports of this study.

To ensure compliance with the protocol, the Coordinating Center will create a MOP that is identical for each site. The MOP will be finalized after the study planning period. The MOP will contain instructions on how to complete all aspects of the study including randomization, measurements, data entry, and a copy of all study forms.

Data collection forms:

- Adverse Event Reporting form – Consists of the AE's with details pertaining to date of event, type of event, related or not, action taken and event outcome.
- Comorbidity Checklist – Questionnaire filled out by the participant at enrollment about their existing medical illness.
- Distal Radius Fracture Complication Checklist and Score Sheet- Form filled out by surgeon (PI) after surgery and every follow up visit, has information on complications developed such as nerve or bone/joint or tendon complications after surgery.
- General Health Questionnaire- information on general health in between follow up visits.
- Hand Edema Form – Measure of fingertip to palmar crease distance.
- Hand Function and Range of Motion data sheet- Measures grip, pinch and wrist range of motion of the injured arm and the normal arm.
- Hand Therapy Data Sheet – Information on type of therapy completed, number of visits, and when therapy was terminated.
- Inclusion/Exclusion Criteria – Includes fracture type and the detailed criteria for eligibility.

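### The adverse-event severity scale ranks events by whether surgery was needed, so a fatal event managed without surgery grades below a hardware removal; separately, the complication comparison between arms has no severity element

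*Protocol*

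**What the plan says.** Section 8.3.3.1 states that "the following guidelines will be used to describe severity" and gives three levels:

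- Mild: "symptoms, no specific treatment"
- Moderate: "diagnostic procedure, specific diagnosis, and/or nonsurgical treatment"
- Severe: "surgical treatment required"

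There is no level above Severe and no other way to reach it. Sections 8.3.5 and 8.3.6 make the site investigators responsible for determining severity, and the protocol offers no second scale. Seriousness is defined separately in 8.3.2 and covers, among other things, death, threat to life and hospitalization.

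The risk list in 2.3.1 includes, for anaesthesia, "slowing or stopping of breathing, failure of the anesthetic or sedation analgesia, cardiac arrest". Under Internal Fixation it includes "Painful hardware requiring removal: RARE".

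For the comparison of complications between arms, section 9.4.2 says that "if the combined complications are rare, we will dichotomize them as present/absent" and fits a logit mixed model. If complications are numerous it uses a count model with a log link. Section 10.1.6.2 lists a surgeon-completed "Distal Radius Fracture Complication Checklist and Score Sheet", which is a different form from the adverse-event form.

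**The concern.** A severity scale should place worse events higher. This one uses the kind of treatment as its yardstick, and in a trial of surgical fixation that yardstick follows the procedure as much as the harm. A medical catastrophe treated without an operation falls in the same class as an infection treated with antibiotics, and below an operation to take out a plate.

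The complication comparison matters because sections 2.1 and 4.1 name a possible excess of complications as the drawback of the volar locking plate. A comparison built only on presence or number cannot tell a reader whether one method's complications more often led to another operation. At stake is how the harms are described, not the efficacy result.

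**Working it through.** The severity scale carries no stated figure to reproduce, so the first step is to apply its wording to events the protocol itself lists.

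**Step 1. Apply the scale in 8.3.3.1.**

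| Event (source) | Treatment assumed | Literal grade | Serious under 8.3.2? |
|---|---|---|---|
| Cardiac arrest under anaesthesia (2.3.1) | nonsurgical | Moderate | yes, life-threatening or fatal |
| Pin-site infection needing antibiotics (2.3.1) | nonsurgical | Moderate | not by itself |
| Removal of painful hardware (2.3.1) | surgical | Severe | not necessarily |

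The first two rows share a grade and the third outranks both. A sudden death with neither diagnosis nor treatment fits no level cleanly.

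**Step 2. Trace where the grade is used.** The 48-hour SAE reporting (8.3.6) depends on seriousness. So does the ad hoc review of deaths (9.4.4). The stopping comparison (9.4.4, repeated in 10.1.1.3) uses rates of serious, related events. No analysis in section 9 uses Mild, Moderate or Severe. The misordering therefore affects the recorded grade and any summary made from it, and nothing else.

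**Step 3. Look for severity in 9.4.2.** The logit model takes presence or absence, and the count model takes a number. Neither has a severity term. If two arms have the same probability of any complication, the present/absent test rejects at about its nominal level (5% for a test at 0.05), whatever proportion of those complications needed surgery.

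**Step 4. What a separate comparison could detect.** The protocol gives no complication rates, so the rates below are assumptions. The formula is the usual normal approximation for two proportions, two-sided 0.05, ignoring clustering:

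power = Φ{ [ |p2 − p1| − 1.96 √(2 p̄(1 − p̄)/n) ] / √( [p1(1 − p1) + p2(1 − p2)]/n ) }, with p̄ = (p1 + p2)/2.

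For p1 = 0.02, p2 = 0.08 and n = 126 (the protocol's expected completers per arm): p̄ = 0.05. The null standard error is √(0.095/126) = 0.0275, and 1.96 times it is 0.0538. The alternative standard error is √(0.0932/126) = 0.0272. Then (0.06 − 0.0538)/0.0272 ≈ 0.23, and the power is 0.59.

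| Assumed rates of complications needing surgery | n = 126 per arm | n = 158 per arm |
|---|---|---|
| 1% vs 6% | 58% | 68% |
| 2% vs 8% | 59% | 69% |
| 2% vs 10% | 77% | 85% |

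So a severe-only comparison would have moderate power against differences of this size. The pooled comparison would have none beyond its error rate if the totals were equal.

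**The case against.** The strongest reply is that severity and seriousness are separate axes and that the protocol protects the one that counts. Deaths and life-threatening events are SAEs, are reported quickly and are reviewed. The stopping comparison is built on serious events. The scale is offered as a guideline, no planned analysis uses it, and the AE and SAE forms as described in 10.1.6.2 record outcome directly and name no severity field. All of that stands, and it limits the point to the grade itself. It does not repair the grade, because investigators are told to determine severity and have only this scale.

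A second reply is that 9.4.2 introduces the rare-event model as an example, and that breakdowns by severity may sit in a statistical analysis plan that is not shown. That is fair. The second half of this point is therefore an inexpensive improvement, not an error.

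Several stronger readings are tempting, and the documents do not support them:

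- *The harm measures as a whole misrank events.* Only the grade does. The complication models flatten severity; they do not reverse it.
- *The faulty grade feeds the complication analysis.* The checklist and the AE form are separate instruments, and nothing says that checklist items carry the 8.3.3.1 grade.
- *The monitoring board will see misleading severity tables.* No such tables are described. Section 10.1.5.2 speaks of lists of events and deaths.
- *A lasting complication is counted at each of the six follow-up visits.* The checklist is completed at each one, but no counting rule says this.
- *The checklist's score is an available severity measure left unused.* Its content is not in the document.
- *The plate would look better on any complication and worse on complications needing surgery.* Rates can be chosen to give that reversal, but the risk list does not support them: antibiotic-treated infection is classed as infrequent for all three methods, plate removal is classed as rare, and tendon rupture is listed for pinning and external fixation only.

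**Conclusion.** The scale in 8.3.3.1 is wrong as written: by its own terms a death or life-threatening event managed without surgery cannot grade above Moderate, while a hardware removal grades Severe. This rests on a literal reading and on taking hardware removal to be a surgical treatment. Its reach is limited to severity grading. SAE reporting, review of deaths, the stopping comparison and the primary efficacy analysis are unaffected.

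The complication comparison in 9.4.2 is conventional but leaves out severity, so a difference between arms in complications needing surgery could go unseen. How large such a difference might be cannot be judged from the protocol. The powers in the working rest on assumed rates and show only that a separate comparison would be informative for differences of about 5 to 8 percentage points.

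**What to change.** In 8.3.3.1, add a life-threatening or fatal level that applies whatever treatment was given, and state that the severity grade is distinct from seriousness under 8.3.2 and does not replace it. Grading every SAE as at least Severe is not needed: it would merge the two axes and rank a brief hospitalization as severe.

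In 9.4.2, keep the any-complication comparison. Beside it, compare arms on complications that needed surgery or met the SAE definition, per patient as present or absent, with the logit mixed model already planned. State that each distinct complication counts once.

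The cost is some wording, re-grading of recorded events from the type, action taken and outcome already on the forms, and one extra table. The severe-only comparison will have fewer events and a wider interval. The amendment history places the current version just before manuscript submission, so the added comparison comes late. It should be labelled supportive and should not take precedence over the planned one.
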